### Participants

The study aims to recruit and enroll 2,260 adults in three inter-related samples in each community: 1) CCMs, 2) CCMs’ friends and family members, and 3) community residents. Extension staff will facilitate the CCs, and in collaboration with the project team, will recruit 10–14 residents to participate in each community’s CC. CCM will be asked to invite friends and family members to participate in the study, and we anticipate a total of 90–112 friends and family members per community to enroll. Approximately 80–100 community residents will also be recruited from each community.

#### Inclusion and Exclusion Criteria

Participants must be at least 18 years of age and English-speaking. Additional eligibility and exclusion criteria for participant groups are shown in Table 1.

**Table 1 Tab1:** Eligibility and exclusion criteria for each type of participant group

**Participant Group**	**Eligibility Criteria**
Change Club Members	•Provide electronic informed consent •Be willing to be randomized to either group •Score “poor” or "intermediate" on at least one of the American Heart Association’s Life’s Simple 7 composite score items •Live in one of the participating communities in New York or Texas
Friends and Family Members	•Provide electronic informed consent •Be a friend or family member identified by a Change Club Member
Community Residents	•Provide electronic informed consent •Live in one of the participating communities in New York or Texas
Extension Educators	•Provide electronic informed consent •Serve as a Change Club leader
**Participant Group**	**Exclusion Criteria**
All Participants	•Cognitive impairment (if it precludes completion of assessments and/or intervention) •Inability to communicate due to severe, uncorrectable hearing loss or speech disorder (if it precludes completion of assessments and/or intervention) •Severe visual impairment (if it precludes completion of assessments and/or intervention) •Inability to read (as it precludes completion of assessments and/or intervention) •Already included in another study sample (e.g., Community Residents cannot also be Change Club Members)

### Recruitment

CC facilitators will attend community events such as school sporting events, fairs, festivals, community meetings, and other emergent recruitment opportunities, as well as drawing upon their extensive network of community contacts to recruit potential participants. CC facilitators will place flyers and posters at community centers, libraries, restaurants, grocery stores, banks, and other relevant locations. We will utilize zip code mailing lists to mail postcards inviting participation to all adult residents in each community up to three times. Other recruitment efforts will include the use of news releases, social media ads, radio ads, and television ads. Targeted digital advertising methods will be utilized to target our ads using zip codes and relevant keywords. A study website was created to help describe the study in further detail and explain the various roles of participation.

#### CCM recruitment

CCM will complete an online eligibility screener and, if eligible, complete an electronic informed consent process. The local extension educator will also communicate with CCMs to discuss the CC activities.

#### Friends and family members recruitment

CCM will be asked to recruit adults in their ‘social circle’ to complete data collection activities using a unique screening link provided to each CCM. Friends and family members invited by a CCM, if interested, will complete an online eligibility screener and, if eligible, complete an electronic informed consent process.

#### Community resident recruitment

Individuals who screen to be CCM and are deemed ineligible, will be invited to participate as community residents. Community residents will complete an online eligibility screener and, if eligible, complete an electronic informed consent process.

### Intervention

County-level extension agents traditionally provide non-formal education and skill-based learning to adults and children in their communities. A local extension educator in each community will be trained to become a CC facilitator to guide stepwise planning workshops, measure engagement, and guide members through nutrition and PA lessons through in-person, virtual, or hybrid methods. CC facilitators will be trained on the CC curriculum and facilitator guide covering all content modules. Once leaders are trained, they will facilitate the first set of CC modules and continue to meet and support their CC thereafter as needed throughout the study. Table 2 shows the multilevel components and summary of the CC curriculum.

**Table 2 Tab2:** Summary of change club curriculum

**Theme 1: Fostering Togetherness and Unity**	
** Module 1:** Introduction	Introduction and program overview
** Module 2:** Fostering Engagement	Engaging in community issues
** Module 3:** Team Building	Working effectively as a team
** Module 4:** Assessing the Community	Assessing local needs and resources
**Theme 2: Identifying Needs**	
** Module 5:** Choosing a Strategy	Deciding on a focus area
** Module 6:** Advocacy Skills	Building capacity for advocacy
** Module 7:** Stakeholder Identification	Identifying and contacting stakeholders
** Module 8:** Asset Mapping	Asset mapping and strength Identification
**Theme 3: Planning for Next Steps**	
** Module 9:** Leadership Skill Building	Leadership development
** Module 10:** Vision Planning	Developing group mission and logic model
** Module 11:** Action Planning	Developing an action plan
** Module 12:** Monitoring and Evaluation	Assessing project outcomes
**Theme 4: Action Part I**	
** Module 13:** Implementation	TBD – based on specific Change Club
** Module 14:** Implementation	TBD – based on specific Change Club
** Module 15:** Implementation	TBD – based on specific Change Club
** Module 16:** Progress Update	TBD – based on specific Change Club
**Theme 5: Action Part II**	
** Module 17:** Implementation	TBD – based on specific Change Club
** Module 18:** Implementation	TBD – based on specific Change Club
** Module 19:** Implementation	TBD – based on specific Change Club
** Module 20:** Progress Update	TBD – based on specific Change Club
**Theme 6: Next Steps**	
** Module 21:** Implementation	TBD – based on specific Change Club
** Module 22:** Implementation	TBD – based on specific Change Club
** Module 23:** Implementation	TBD – based on specific Change Club
** Module 24:** Closing and Wrap-Up	Program Conclusion

The first set of modules include building group rapport and identity and establishing group norms. CC members will engage in online modules outside of meetings that discuss nutrition and PA topics, with a focus on social and environmental barriers and facilitators. During each meeting, facilitators will encourage members to share what they have learned and how they are implementing individual-level change. During the subsequent modules, which focus on issue identification and action planning phases, CCs will conduct an assessment of community assets [84], review a menu of possible built environment changes, and select one or more that can feasibly be implemented in the community within six months. To maximize potential for effectiveness, menu options: 1) are recommended by the Community Preventive Services Task Force [85]; 2) earned a Class I or a Class II rating from the American Heart Association as population approaches to improve diet or PA behavior, indicating the weight of the evidence for the intervention is in favor of efficacy [86]; and/or 3) are recommended by the Global Action Plan for the Prevention and Control of Noncommunicable Diseases [87].

### Participant retention

We will implement multiple common and effective retention strategies, including participation tracking procedures, using multiple contact methods, an accessible phone number for support, keeping in regular contact, highlighting the benefits of research, and using validated surveys [88–93]. We will send notifications via phone, email, text, and/or postal mail to participants at regular intervals, which has worked well to minimize attrition in our prior rural community intervention studies. These notifications may include non-religious holiday (e.g., New Year) or seasonal (e.g., ‘Welcome back, Spring!’) postcards, and messages via email, text, and phone related to upcoming data collection. We have had success retaining participants (80–95% retention) in prior studies with similar populations and timeframes [94].

### Participant compensation

Participants will be compensated $75 at each study timepoint (baseline, 12 months, 24 months, and 36 months) for completing the following: online survey, 24-h dietary recall, and self-reported pedometer or wearable fitness tracker readings. Participants who complete all data collection activities across the four timepoints will be provided an additional bonus at the end of the study ($150 for CCM and $75 for friends and family members and community residents). Some participants will be invited to complete data collection for process evaluation. Additional compensation for those activities is detailed in Table 5. All compensation will be given in the form of an electronic gift card or through a mobile payment app.

### Outcome assessment

Outcome data will be collected via online survey which will include self-measurement of height, weight, and waist circumference; a 24-h dietary recall collected via the Automated Self-Administered 24-h Dietary Assessment Tool (ASA24) [95]; and self-reported pedometer or wearable fitness tracker readings. Survey data will be collected using the Qualtrics application. All data will be coded using participant identification numbers instead of participant names. Only the Principal Investigator and the research staff will have access to the list that matches the names with the participant identification number. Data will be stored in a secure central location and access to files will be restricted to specific study staff. The contents of identifiable data files will be encrypted to secure data. SimpleStep Rechargeable Step Counters (Pedometer Express_,_ Cedar Minnesota, USA) or a wearable fitness tracker owned by the participant (e.g., Fitbit) will be used to obtain objective data on participant PA. The participant-owned fitness tracker must be comparable to the pedometer provided by the project (e.g., 3D motion sensor). Pedometers will be worn for seven days at each time point. Participants will record their daily steps and then report them to attain valid and reliable estimates of participants’ average daily PA.

LS7 score at 24-month follow-up is the primary efficacy endpoint. LS7 is a 7-item composite cardiovascular health score correlated with prevalence of cardiovascular disease events [96, 97]. Each item is classified as poor (0), intermediate (1), or ideal (2) (see Table 3). Scores for each of the seven items are summed for a total LS7 score between 0 and 14, with higher scores indicating better health.

**Table 3 Tab3:** American Heart Association’s Life’s Simple 7 components and scoring

Indicator	Poor (0)	Intermediate (1)	Ideal (2)
Smoking	current smoker	quit < 12 months ago	never smoked or quit > 12 months ago
BMI	obese (> 30)	overweight (25–29.9)	healthy weight (< 25)
Physical activity	none	some (1–149 min/week of moderate or 1–74 min/week of vigorous)	recommended amount (≥ 150 min/week of moderate or ≥ 75 min/week of vigorous)
Healthy diet indicators met • ≥ 4.5 cups/day of FV • ≥ 2 servings/week of fish • ≥ 3 servings/day of whole grains • ≤ 36 oz/week of sugar‐sweetened beverages • ≤ 1500 mg/day of sodium	0 or 1 indicators	2 or 3 indicators	4 or 5 indicators
Cholesterol	high (≥ 240 mg/dL)	borderline high (200–239 mg/dL) or normal with medication	normal (< 200 mg/dL)
Blood pressure	high (≥ 140 mmHg systolic or ≥ 90 mmHg diastolic) or diagnosed with coronary heart disease, heart attack, heart failure, stroke, vascular disease, or congenital heart defects	elevated (120–139 mmHg systolic or 80–89 mmHg diastolic) or normal with medication	normal (< 120 mmHg systolic and < 80 mmHg diastolic)
Glucose	diabetes (≥ 126 mg/dL)	prediabetes (100–125 mg/dL) or normal with medication	normal (< 100 mg/dL)

Assessment of secondary outcomes will also focus on the 24-month follow-up timepoint. There are 24 secondary outcomes at the individual level, two of which are objective values (see Table 4). In addition, there are six outcomes at the community/collective level (e.g., social cohesion, community investment, civic engagement) and six outcomes at the environmental level (e.g., neighborhood safety, food availability, walking environment), all of which are assessed with tools adapted from validated instruments.

**Table 4 Tab4:** Data collection schedule

Data	Measure	Before baseline	Baseline	+ 12 months	+ 24 months	+ 36 months
Electronic informed consent	Institutional Review Board-approved consent	X				
Sociodemographics	Sociodemographic questions [98]		X			
Adverse event monitoring	Standard monitoring		X	X	X	X
Social determinants of health	Questions adapted from Billioux et al. [99] and Gadhoke et al. [100]		X	X	X	X
Food security	Brief assessment [101]		X	X	X	X
Social network characteristics	Social network questions [102]		X	X	X	X

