**Secondary outcomes—individual**						
BMI^a^	Self-measured		X	X	X	X
Waist circumference (in)	Self-measured		X	X	X	X
High/elevated blood pressure (y/n)^a^	Classified from self-reported measurements, diagnosis, and medication use		X	X	X	X
High/borderline total cholesterol (y/n)^a^	Classified from self-reported measurements, diagnosis, and medication use		X	X	X	X
Diabetes/pre-diabetes (y/n)^a^	Classified from self-reported measurements, diagnosis, and medication use		X	X	X	X
General health status	SF-36 general health item [105]		X	X	X	X
Current smoker (y/n)^a^	LS7 item [103, 104]		X	X	X	X
Total HEI score (1–100)	Single 24-h recall collected via the ASA24 [95]		X	X	X	X
Total fruit and vegetable intake (cups/day)^a^	LS7 item [103, 104]; ASA24 [95]		X	X	X	X
Consumption of whole grains (servings/day)^a^	LS7 item [103, 104]; ASA24 [95]		X	X	X	X
Fiber intake (g/day)	DSQ [106, 107]; ASA24 [95]		X	X	X	X
Met recommendation for fish consumption (y/n)^a^	LS7 item [103, 104]		X	X	X	X
Consumption of ultra-processed foods (% total kcal)	ASA24 [95]		X	X	X	X
Frequency of consuming ultra-processed foods (times/month)	Adapted from DSQ [106] and BSQ2 (9 items) [108]; ASA24 [95]		X	X	X	X
Red and processed meat consumption (g/week)	Estimated from DSQ [106, 109]; ASA24 [95]		X	X	X	X
Alcohol consumption (drinks/day)	Adapted from the AUDIT (2 items) [110]; ASA24 [95]		X	X	X	X
Total steps per day	Average of self-reported pedometer or wearable fitness tracker readings		X	X	X	X
Total physical activity (MET-min/week)^a^	IPAQ-long [111]		X	X	X	X
World Cancer Research Fund/American Institute for Cancer Research recommendation adherence score (0–7)	Composite [112]		X	X	X	X
Healthy eating motivation (1–5)	Adapted Naughton & McCarthy Healthy Eating Motivation Scale (3-items) [113]		X	X	X	X
Confidence for healthy eating (1–5)	Adapted from Sallis Eating Habits Confidence Survey and Seguin-Fowler Expanded Eating Habits Confidence Survey (7-item) [114, 115]		X	X	X	X
Social support for healthy eating (1–5)	Ball Social Support for Healthy Eating Scale [116]		X	X	X	X
Exercise attitudes (1–5)	Adapted from Sect. 2, question 5 of the AARP Exercise Attitudes and Behaviors Survey (4 items) [117]		X	X	X	X
Exercise confidence (1–5)	Adapted from Sallis Exercise Confidence Survey (3 items) [115]		X	X	X	X
Social support for physical activity (1–5)	Ball Social Support for Physical Activity Scale [116]		X	X	X	X

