### Statistical analysis

#### Sample size determination

Our sample size targets are based upon the ability to detect significant difference between arms at the 24-month post-baseline time period using a t-test, with a desired power of 80%, an alpha level of 0.05, and a two-sided test. The sample size requirements for this study are based on our prior intervention studies [132, 133], which were six months in length and demonstrated an effect size of + 0.7–0.8 units in the LS7 composite score. We aim to recruit 70 CCM in intervention and 70 in control and, based on our prior CC work [133], we estimate 10% attrition each year, resulting in 57 CCM in each arm at 24-month follow-up. Cluster sizes were assumed to be consistent across communities, and the intraclass correlation of participants within those clusters is estimated to be 0.025. This adjustment results in an effective sample size of 45 CCM per arm and an ability to detect an effect size of 0.60 SDs (approximately 1 unit in the LS7 composite score).

We will enroll 560 friends and family members in intervention communities and 560 in control communities but anticipate greater attrition (20% per year) and larger clustering of friends and family members around CCM and within communities (ICC = 0.08). The effective sample size will be 252 friends and family members per arm at 24-month follow-up, and an ability to detect an effect size of 0.25 (approximately 0.4 change in LS7 composite score).

We also will enroll 400–500 community residents in intervention communities and 400–500 in control communities. We estimate 20% attrition per year among community residents and an ICC of 0.025, resulting in an ability to detect an effect size of 0.36 (mid-way between the effect sizes detectable in CCM and friends and family members samples).

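### The Table 3 activity item of the primary LS7 score never adds moderate and vigorous minutes, so some more active people score lower; BMI 30.0 and a 12-month quit have no class

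*Protocol article*

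**What the plan says.** The Outcome assessment section of the protocol article states: "LS7 score at 24-month follow-up is the primary efficacy endpoint". On scoring it says "Each item is classified as poor (0), intermediate (1), or ideal (2) (see Table 3", and then "Scores for each of the seven items are summed for a total LS7 score between 0 and 14". Table 3 is therefore the scoring rule for the primary endpoint.

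In the physical-activity row, no activity scores 0. A score of 1 goes to "some (1–149 min/week of moderate or 1–74 min/week of vigorous" minutes, and a score of 2 to "recommended amount (≥ 150 min/week of moderate or ≥ 75 min/week of vigorous" minutes. The row has no combined term.

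Two other rows have open boundaries. BMI is poor above 30 and intermediate from 25 to 29.9. Smoking is intermediate for a quit under 12 months ago and ideal for a quit over 12 months ago.

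Table 4 lists "Total physical activity (MET-min/week" from the long IPAQ as a secondary outcome and marks it as an LS7 component. The article does not say that this total sets the 0/1/2 class. The item classes are also used at entry: a Change Club member (CCM) must be poor or intermediate "on at least one of the American Heart Association’s Life’s Simple 7 composite score items".

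**The concern.** The activity row sets 75 vigorous minutes level with 150 moderate minutes, yet gives no credit for a mixture of the two. A person can pass the table's own recommended equivalent by a wide margin and still be classed as doing only some activity, while a less active person is classed as ideal. Physical activity is a direct target of the intervention, and the item feeds the primary endpoint.

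This goes beyond the coarseness of any three-level item. The threshold is crossed by the table's own equivalence and the crossing is not scored. The BMI and smoking gaps are smaller, but they leave the analyst to choose a class where the table gives none.

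**Working it through.** **1. Yardsticks.** The sample-size section plans "with a desired power of 80%, an alpha level of 0.05, and a two-sided test". For CCM per arm:

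- Retained at 24 months: 70 × 0.9² = 56.7 (stated as 57).
- Per community: 56.7 / 5 = 11.34.
- Design effect: 1 + (11.34 − 1) × 0.025 = 1.2585.
- Effective size: 56.7 / 1.2585 = 45.05 (stated as 45).
- Detectable effect: (1.960 + 0.842) × √(2/45) = 0.591 SD, or 0.597 SD by the noncentral t (stated as 0.60 SD, about 1 LS7 unit).

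The CCM figures reproduce and are not in question here. The stated 1 unit (CCM) and 0.4 unit (friends and family) serve below only as yardsticks.

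**2. The printed rule against a combined rule.** Let M and V be weekly moderate and vigorous minutes. The combined rule uses M + 2V; the weight 2 is 150/75, from the table itself.

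| M | V | M + V | M + 2V | Printed class | Combined class |
|---|---|---|---|---|---|
| 150 | 0 | 150 | 150 | 2 | 2 |
| 0 | 75 | 75 | 150 | 2 | 2 |
| 140 | 0 | 140 | 140 | 1 | 1 |
| 140 | 70 | 210 | 280 | 1 | 2 |
| 149 | 74 | 223 | 297 | 1 | 2 |
| 100 | 50 | 150 | 200 | 1 | 2 |
| 160 | 30 | 190 | 220 | 1 and 2 | 2 |
| 30 | 90 | 120 | 210 | 1 and 2 | 2 |

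The pair 149 + 74 scores below 150 + 0 even in raw minutes (223 against 150), so the reversal does not depend on the weight. Moving from 140 + 0 to 140 + 70 doubles moderate-equivalent activity and leaves the printed score at 1.

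**3. How much of the scoring grid is affected.** There are 150 × 75 = 11,250 whole-minute pairs with M ≤ 149 and V ≤ 74. Of these, 5,550 (49.3%) have M + 2V ≥ 150 and would move up a class. With plain addition, M + V ≥ 150, the figure is 24.7%. These are shares of a grid, not of participants.

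**4. Overlap.** On the grid of 0–300 by 0–150 minutes (301 × 151 = 45,451 pairs), 22,498 pairs meet both the score-1 and the score-2 wording, and none meets neither.

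**5. Boundaries.** A BMI of 30.0 is neither within 25–29.9 nor above 30. A quit at exactly 12 months is neither under nor over 12 months. If BMI were normal with mean 29–30 and SD 6–7 (an assumption), 29.9–30.0 would hold about 0.57–0.66% of people.

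**6. Effect on the arm difference.** Let p be the share in an arm at 24 months who score 2 by the combined rule and 1 by the printed rule. Leaving aside baseline adjustment and with equal shares at baseline:

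arm difference (combined) − arm difference (printed) = p(intervention) − p(control).

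The article gives neither share. As assumptions: if 2–20% of a sample were affected, its mean would shift by at most 0.02–0.20 units. If the shares differed between arms by 5–10 percentage points, the arm difference would shift by 0.05–0.10 units, which is 5–10% of 1 unit or 12.5–25% of 0.4 units. Equal shares give no shift.

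The sign is open too:

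- 140 + 0 to 140 + 70: the printed score stays at 1; the combined score goes from 1 to 2. The printed rule shows less gain.
- 140 + 20 to 150 + 20: the printed score goes from 1 to 2; the combined score is 2 at both visits (180, then 190). The printed rule shows more gain.

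**The case against.** The strongest reply is that Table 3 condenses a score defined elsewhere. Table 4 gives the composite by citation, and the full protocol or the cited source may say how mixed minutes combine. That may be so, but the article does more than stay silent. It prints minute cut-offs, says items are classified by that table, and joins the two intensities by an or. Conjunctions carry meaning in this table: the blood-pressure row requires both limits for normal and either limit for elevated. The reversal is in the rule as stated.

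Other replies stand wholly or in part:

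- **Overlap.** A reader might infer that 160 + 30 cannot be scored. The columns run from none through some to the recommended amount, and the natural reading gives the higher class. The reversal remains under that reading.
- **Boundaries.** At one decimal, only a BMI of 30.0 is unassigned. The gaps are real but small.
- **Eligibility.** A reader might infer that CCM selection is distorted. One non-ideal item out of seven is enough for entry, so the activity class decides only for someone ideal on the other six. The effect is negligible.
- **Other outcomes.** Total activity and daily steps are secondary outcomes and capture mixed activity. They do not repair the primary score.

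**Conclusion.** The point holds for the rule as printed. The activity item misclassifies, by 1 of 14 points, anyone who passes the table's own recommended equivalent only by mixing intensities, and two boundary values have no class. This is certain from the text and needs no outside source.

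The consequence for the trial result is not established. A reader might infer that the rule pulls the arm difference towards zero. The documents do not support this, because plausible changes in activity move the comparison either way and the article gives neither the baseline mix nor how activity will change. A reader might also set the 1-point error beside the 1-unit detectable CCM effect. That compares one person's score with a difference between means; only a difference between arms in the share affected matters. The 12.5–25% of the friends-and-family target rests wholly on an assumed 5–10 point imbalance. The effect is probably modest.

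The rule should still be corrected before outcomes are analysed, so that the scoring of a primary-endpoint item is not chosen afterwards.

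**What to change.** - Score the activity item on moderate + 2 × vigorous minutes per week, in whole minutes: 0 = poor, 1–149 = intermediate, 150 or more = ideal. This also removes the overlap within the row.
- Do not add a table-wide rule that the highest class met applies. In the cholesterol and glucose rows, a person treated to normal levels meets both the intermediate and the ideal wording, and there the lower class is evidently meant.
- Write BMI as < 25, 25 to < 30, and 30 or more. Write smoking as quit < 12 months against 12 months or more.
- Apply the same scoring at every time point.
- Confirm that the LS7 activity item and the online screener each record moderate and vigorous minutes separately. The long IPAQ is scheduled from baseline, but the article does not say that it supplies this item or the screening data.
- Report the printed rule as a sensitivity analysis.

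The cost is a change of scoring syntax and the check of the instruments. There is a slight loss of comparability with the earlier studies behind the planning effect of 0.7–0.8 units, if they used the printed rule; the sensitivity analysis covers that.
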